**Orthodontic factors**
Full upper and lower arch orthodontic fixed appliance.Extraction of bilateral upper and lower permanent first or second premolars at least 2 weeks before bond-up.No previous orthodontic treatment.
**
*Exclusion criteria*
**
Craniofacial deformities.Mental or physical disability leading to impaired manual dexterity and difficulty comprehending and following oral hygiene instructions.Underlying chronic medical illness, oral diseases.
**
*Withdrawal criteria*
**
Participants are free to withdraw anytime during the period of study. Reasons for withdrawal will be noted down. Possible criteria of withdrawal include:Serious adverse events arising from laceback, which is very unlikely as it has not been reported in literature.Participant not following study procedures.Participant unwilling to continue orthodontic treatment.

An intention-to-treat analysis is used, whereby data from all participants is analyzed irrespective of any subsequent withdrawal or protocol deviation to ensure that the results will reflect the effects of laceback in a real-world setting, while maintaining the study power because no participants are omitted from the analysis [20,21]. Repeated measures data for plaque score and pain score will be analyzed using a mixed model for repeated measures (MMRM), which accounts for within-participant correlation and handles missing data without formal imputation under the missing at random assumption [22].

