### Sample Size Calculation

The sample size is determined using G*Power (Version 3.1.9.6, Heinrich Heine University, Düsseldorf, Germany). To assess the effect of laceback on a patient’s oral hygiene, a previous split-mouth study using the Orthodontic Plaque Index (OPI) to record plaque score on orthodontic patients will be used in this study [23]. By referring to the SEM and sample size (n) reported in that study, the SD of OPI is calculated to be 1.88 by applying the formula $SD=SEM\times \sqrt{n}$. A difference of 1 point in OPI was deemed clinically meaningful to be detected. A total of 34 participants are needed for 68 sites (34 laceback and 34 no laceback), which would give a power of 85% with a significance level of 0.05 to detect a 1-unit difference in OPI score. Assuming a 10% dropout rate, 38 participants are recruited, providing a total of 76 sites (38 laceback and 38 no laceback).

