### Intended Statistical Analysis

Statistical analysis is conducted using IBM SPSS Statistics (version 31). Descriptive statistics are used to report participant demographics, baseline characteristics, and frequency of laceback complications. To assess whether the data are normally distributed, interpreting the shape of the histogram and the Shapiro-Wilk test are used. Intra- and interrater reliability for plaque score assessment are measured using Cohen kappa. The threshold for good inter- and intrarater reliability is set to be more than 0.8.

Repeated outcome measurements of plaque scores will be analyzed using a mixed model for repeated measures. The model includes treatment group, time, and treatment-by-time interaction as fixed effects, with participant included as a random effect. A mixed model for repeated measures allows inclusion of participants with incomplete follow-up data without requiring formal imputation, assuming data are missing at random. If the data are not normally distributed, plaque scores over time (T_0_, T_1_, and T_2_) will be compared using the Friedman test.

From the pain diary gathered, the pain scores are plotted against time to allow calculation of area under the curve (AUC) using the trapezoidal rule [34]. Pain AUC will be calculated between T_0_ and T_1_ and T_1_ and T_2_. The mean pain AUC for laceback and no laceback sides will be calculated by averaging pain AUC values between T_0_ and T_1_ and between T_1_ and T_2_. To compare differences in mean pain AUC of laceback and no laceback groups, a paired *t* test is used if data are normally distributed. If the normality assumption is violated, the Wilcoxon signed-rank test is applied instead.

The mean frequency of archwire complications is recorded by summing up the number of complications that happen throughout the study period from T_0_ to T_2_. To compare differences in the mean frequency of archwire complications between the laceback and no laceback groups, a paired *t* test is used if data are normally distributed. The mean frequency of laceback complications and the number and percentage of participants with at least 2 laceback complications are also reported. The value of *P*<.05 is considered statistically significant.

Sensitivity analysis will be conducted by comparing the results of intention-to-treat and per-protocol analyses. If both analyses yield similar results, this demonstrates the robustness and validity of the study’s conclusions.

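### Agreement between the intention-to-treat and per-protocol results is said to demonstrate validity, but it shows only insensitivity to excluding measured deviators and cannot reveal bias common to both analyses

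*Protocol article*

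**What the plan says.** Intended Statistical Analysis ends with the sensitivity plan: "Sensitivity analysis will be conducted by comparing the results of intention-to-treat and per-protocol analyses". The next sentence gives the rule for reading it: "If both analyses yield similar results, this demonstrates the robustness and validity of the study’s conclusions". The article does not say how close the results must be to count as similar, and it does not define the per-protocol set.

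The intention-to-treat analysis is described after the withdrawal criteria in Textbox 1: "data from all participants is analyzed irrespective of any subsequent withdrawal or protocol deviation". The same paragraph says that the mixed model "handles missing data without formal imputation under the missing at random assumption", and Intended Statistical Analysis repeats that it "allows inclusion of participants with incomplete follow-up data without requiring formal imputation, assuming data are missing at random". The model itself is specified as follows: "The model includes treatment group, time, and treatment-by-time interaction as fixed effects, with participant included as a random effect".

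**The concern.** The rule has one input, whether two overlapping analyses look alike, and one output, a declaration that the conclusions are valid. Two features of this trial limit what that input can show.

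- **Lost participants are absent from both analyses.** A missed visit in a split-mouth trial loses both sides together. With no imputation, that participant has no side difference at that visit to contribute, whichever analysis set is used.
- **Non-adherence can also lead to absence from both.** The withdrawal criteria list failure to follow study procedures as a possible reason for withdrawal. A deviator withdrawn on that ground leaves no later scores in the intention-to-treat analysis either.

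The two estimates can therefore differ mainly through deviators who stayed and were measured. If those who leave have a larger laceback-side plaque excess than those who stay, both analyses understate the effect by a similar amount and still agree. A null or small plaque effect could then be called valid by a check that never touched the assumption on which the primary analysis rests.

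**Working it through.** **Inputs from the article (Sample Size Calculation).** "the SD of OPI is calculated to be 1.88"; "A difference of 1 point in OPI was deemed clinically meaningful to be detected"; 85% power; significance level 0.05; 34 participants needed; 10% dropout; 38 recruited.

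**Step 1: reproduce the stated figure.** Paired t test, two-sided 0.05, difference 1, SD of the side difference 1.88: n = 34 gives power 85.3%. Inflation: 34 / 0.9 = 37.8, so 38. Both figures reproduce, so 1.88 is used below as the SD of the side difference, and the planned loss is 38 - 34 = 4 participants.

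**Step 2: what a lost participant contributes.** With participant as the only random effect and both sides scored or missed together, the side contrast at a visit equals the mean of the within-participant side differences at that visit. A participant without that visit drops out of the mean. As a check, three data sets of 38 were generated, the 4 largest T2 side differences were removed, and the mixed model was fitted.

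| Data set | Full data | Intention-to-treat | Per-protocol (completers) |
|---|---|---|---|
| 1 | 1.2079 | 0.8809 | 0.8809 |
| 2 | 0.5713 | 0.2305 | 0.2305 |
| 3 | 0.6600 | 0.3390 | 0.3390 |

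The two planned analyses coincide, and both are 0.32 to 0.34 points too low.

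**Step 3: shared bias at the planned loss.** If the 4 lost participants have a laceback-side excess larger by e than the rest, the mean over all 38 is higher than the mean over the 34 by e × 4/38. The bias in both analyses is therefore -e × 4/38. The article gives no value for e, so a range is shown.

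| Assumed e (OPI points) | Bias in both analyses |
|---|---|
| 0.5 | -0.05 |
| 1.0 | -0.11 |
| 2.0 | -0.21 |

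**Step 4: gap between the two analyses.** Assume a correlation of 0.5 between the T1 and T2 side differences. The SD of a participant's average is then 1.88 × √((1 + 0.5)/2) = 1.63. If per-protocol drops k further participants at random from the 34, the SD of the gap is 1.63 × √(1/(34 - k) - 1/34), and the mean absolute gap is √(2/π) = 0.80 times that.

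- k = 0: gap 0.
- k = 2: SD 0.070, mean gap 0.06.
- k = 4: SD 0.102, mean gap 0.08.

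Simulation with these settings gave the same gaps with and without the 2-point excess, and a bias of -0.21 in both analyses. Agreement in the verdict at P<.05 with no true effect was 100%, 98% and 97% (k = 0, 2, 4), whether or not the excess was present. At a true effect of 0.5 it was 100%, 92% and 88%, again the same with and without it.

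**Step 5: where the comparison does work.** Suppose instead that nobody is lost, the true effect is 1, and per-protocol removes k of 38 deviators who show none of the effect. Take similar to mean within 0.25 OPI (an assumption). The expected gap is k/38 × 1, with SD 1.88 × √(1/(38 - k) - 1/38).

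| k | Expected gap | SD of gap | Agree, deviators unrelated to outcome | Agree, deviators lose the effect |
|---|---|---|---|---|
| 4 | 0.105 | 0.105 | 98% | 92% |
| 8 | 0.211 | 0.157 | 89% | 60% |

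Other outcome-related mechanisms gave 90 to 92% at k = 4 and 41 to 60% at k = 8.

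**The case against.** **The comparison is being tested on a bias it is not meant to find.** This is fair. An intention-to-treat versus per-protocol comparison addresses deviations, and Step 5 shows that it responds when deviations are frequent and tied to outcome. A reader might infer that the rule is met equally often whether or not the result is biased. The documents do not support that. It holds for bias common to both analyses, not for bias that the deviations themselves cause.

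**The overlap of the two sets is inferred.** This stands too. Interventions Common to Both Groups sets several rules that participants could break and still be measured (extra hygiene aids, professional cleaning, brushing before visits). The Results section records no deviations so far, but only 14 participants had completed. A participant with T1 but not T2 could also enter one analysis and not the other. A richer covariance structure would make the estimates close rather than identical. If the effect is read as change from T0, the baseline scores of lost participants enter one analysis only, but they carry no information on the unseen follow-up plaque.

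**The 2-point scenario is extreme.** Agreed: it is half of the 0 to 4 scale, and the resulting 0.21 is about a fifth of the 1-point target. General poor hygiene among those who leave would not bias a side contrast. The loss must track the difference between sides.

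**Other sensitivity analyses may be in the full plan.** A reader might fault the article for describing no analysis that departs from missing at random. That omission is no fault, because Clinical Trial Registration says that the intended statistical analysis plan is held on the registry. The point concerns the stated inference, which further analyses elsewhere would not make true.

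**The limitations are discussed elsewhere.** The Discussion names the lack of participant and clinician blinding among others, but this does not withdraw the claim that agreement demonstrates validity.

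**Conclusion.** The sentence is wrong as an inference. Similar results show insensitivity to excluding protocol deviators who were still measured. They do not demonstrate validity, because bias common to both analyses leaves the agreement intact. At the planned loss of 4 of 38, a 2-point laceback-side excess among those lost would bias both estimates by about -0.21 OPI, with an average gap between them of only 0 to 0.08. Smaller excesses scale down in proportion.

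These figures rest on 1.88 as the SD of the side difference, an assumed T1 to T2 correlation of 0.5, no follow-up scores for the 4 lost, and 0 to 4 further random per-protocol exclusions. The size of the excess is an assumption, not a forecast. The correction should be made, since it governs what the trial may claim about its conclusions.

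**What to change.** 1. Replace the sentence with one of this kind: similar results indicate that the conclusion is insensitive to excluding protocol deviators. Keep the per-protocol analysis as supportive.
2. Test missing at random directly. Impute the missing T1 and T2 side scores under the mixed model, shift the imputed laceback-side scores by 0.5, 1.0, 1.5 and 2.0 OPI points (capped at the scale maximum of 4), and report the shift at which the primary conclusion changes.
3. When interpreting that tipping point, say how plausible such a shift is on a 0 to 4 scale, and do not declare the result valid from agreement alone.

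The cost is a wording change and a small extra analysis, with no new data or participants. Recruitment is planned to June 2027 and the primary analysis to October 2027, so this can still be fixed before the data are analysed. The downside is that the trial may have to report that its conclusion depends on a few missing participants.

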### Adverse Events

Some common complications during orthodontic fixed appliance treatment using laceback ligatures include pain, discomfort, and appliance breakage. These complications rarely require termination of orthodontic treatment and can be managed effectively using analgesics, orthodontic wax, and repairing the broken appliances when the situation arises. Nevertheless, an adverse events reporting form is prepared in case it is required by any of the study participants. During T_1_, T_2_, and emergency appointments, archwire and laceback complications are assessed, and any severe unintended harms beyond those listed in the protocol are recorded by the assessors. If a severe adverse event occurs, the laceback intervention is terminated for the participant. Further orthodontic management of the participant will be taken over by the treating clinician.

### Monitoring

A data monitoring committee is not deemed necessary for this study as it is of minimal risk. Trial monitoring is done on a 6-month basis through a research progress presentation conducted by the Research Management Committee of IIUM.

## Results

Ethical approval was granted by the IIUM Research Ethics Committee (IREC-2026‐582) in January 2026. Funding was secured through the IIUM Kulliyyah of Dentistry Postgraduate CHAIN Grant (CHAIN 26-014-0014) in the same month. Participant recruitment commenced in February 2026 with a planned completion date of June 2027. To establish measurement reliability, interrater and intrarater agreements were evaluated using Cohen kappa. Interrater reliability was calculated between 3 examiners ([name], [name], and SR) and a gold-standard examiner ([name]). The interrater Cohen kappa values ranged from 0.801 to 0.804. Intrarater reliability for each examiner demonstrated strong reproducibility, with Cohen kappa values ranging from 0.806 to 0.862.

The primary analysis is scheduled for completion by October 2027. Regardless of outcome, a paper reporting the primary results will be submitted for publication in a peer-reviewed orthodontic journal by June 2028. As of the submission of this protocol paper, 24 participants have been enrolled and 14 have completed all data collection visits. No deviations from the original protocol have been recorded.

## Discussion

This protocol describes a single-center, single-blind, split-mouth randomized controlled trial designed to evaluate the clinical and patient-reported outcomes of passive laceback ligatures during the alignment phase of orthodontic fixed appliance treatment. Existing evidence on laceback is almost entirely confined to its effects on incisor inclination and molar anchorage. A systematic review and meta-analysis found that laceback produced only a clinically negligible 0.50-mm incisor retroclination and a nonsignificant 0.45-mm greater molar mesialization compared to controls [5]. In that review, the authors explicitly flagged the absence of data on oral hygiene, appliance breakages, and pain as critical gaps warranting future investigation. This trial directly addresses all three of those gaps, making it the first RCT to do so within a single, methodologically controlled study. In contrast to prior studies, which used parallel-group designs and cephalometric outcome measures, this protocol uses a split-mouth design and focuses exclusively on outcomes that have been identified as both clinically meaningful and patient-relevant.

Based on the null hypothesis that laceback will not produce statistically significant differences in clinical and patient-reported outcomes, we anticipate that this trial may reveal that passive laceback ligatures are associated with modestly elevated plaque scores compared to the no-laceback side, reflecting the additional plaque-retentive surface created by the figure-of-eight ligation pattern. We hypothesize that the laceback side may also demonstrate a lower frequency of archwire complications, lending quantitative support to the widely held but as yet unverified clinical belief that lacebacks help stabilize flexible archwires against masticatory forces. With respect to pain, we hypothesize that the laceback side may be associated with a small but measurable increment in discomfort, particularly in the early weeks following placement, which may have implications for patient counseling.

When laceback was first introduced, it was intended to counteract the mesial crown tip of the canine bracket and prevent labial segment proclination during the leveling and alignment phase of preadjusted edgewise therapy. Although the effectiveness of laceback in controlling the anteroposterior position of the labial segment has since been disputed, it continues to be used by clinicians for several other purposes, most notably the protection of flexible initial archwires from masticatory forces [6]. The role of laceback in supporting the main archwire, however, remains largely anecdotal. If laceback is demonstrated to reduce the frequency of archwire breakage and dislodgement, it may serve as a valuable tool in minimizing treatment disruptions and unplanned emergency appointments, both of which impose additional costs and inconveniences on patients and clinicians alike. Conversely, if it does not meaningfully contribute to archwire stability, the justification for its routine use would need to be reconsidered.

Orthodontic fixed appliances and their auxiliaries are recognized as plaque-retentive environments, providing additional surface area for biofilm formation and impeding effective oral hygiene. Maintaining adequate oral hygiene is of paramount importance during fixed appliance therapy to minimize iatrogenic complications such as enamel demineralization, dental caries, and periodontal deterioration [35,36]. By evaluating the effects of laceback on a patient’s oral hygiene, this research will provide valuable insights to help clinicians decide whether additional oral hygiene instructions or preventive measures are necessary when using laceback. This will benefit patients by ensuring good oral health throughout the treatment process and contributing to improved overall treatment outcomes.

Furthermore, pain and discomfort are common concerns during orthodontic fixed appliance treatment. As an additional appliance component in direct contact with the canine bracket and molar hook, laceback may contribute to soft tissue irritation, altered force distribution, and heightened sensitivity, particularly during the first days after placement. However, the specific contribution of laceback to pain during the alignment phase has not previously been investigated, leaving clinicians without evidence to inform patient counseling at the time of consent.

This study also reflects the broader shift in orthodontic research toward patient-reported outcome measures as primary or coprimary endpoints. Recent studies have emphasized that orthodontic evidence should prioritize outcomes that are directly meaningful to patients, not merely clinician-assessed clinical indices [37-39]. By incorporating pain and discomfort as primary endpoints alongside plaque score and appliance complication rates, this trial provides the more comprehensive evidence base required for evidence-based clinical decision-making and patient-centered consent.

Key strengths of this protocol include its randomized split-mouth design, which controls for patient-level confounders; the use of validated and orthodontically appropriate outcome measures (OPI for plaque and Visual Analog Scale for pain); standardized laceback placement verified against a study model prior to commencement; blinded plaque score assessment; and prospective trial registration (ClinicalTrials.gov ID: NCT07039071). The split-mouth design is particularly advantageous in this context because the intervention is strictly localized: the presence of a laceback on 1 side of the mouth does not mechanically or biologically influence plaque accumulation, archwire stability, or pain on the contralateral side, thereby satisfying the key prerequisite for a valid split-mouth trial with negligible carry-across effect.

Several limitations should be acknowledged. First, the single-center nature of this study, conducted within a specialist postgraduate orthodontic clinic, may limit generalizability to primary care settings or to practices using different bracket systems or prescriptions. Second, the inability to blind participants or the treating clinician to the intervention side is an inherent limitation of the split-mouth design; this risk has been partially mitigated by implementing blinded plaque score assessment. Third, the 8-week follow-up period may not capture longer-term changes in oral hygiene adaptation or pain habituation. Fourth, the use of a single operator for laceback placement enhances consistency and reproducibility within this trial, but may restrict external validity across different clinical hands. These limitations will be transparently reported in the subsequent efficacy paper and will be considered carefully during interpretation of results.

If significant effects of laceback on oral hygiene or pain are demonstrated, future work should explore whether targeted patient education delivered at the time of laceback placement can mitigate these adverse effects. Multicenter replication across different clinical settings, bracket systems, and operator experience levels would strengthen external validity and test the generalizability of these findings. Future trials might also extend the follow-up period beyond 8 weeks to encompass the full alignment and leveling phase and to determine whether adverse effects on oral hygiene or pain attenuate over time as patients adapt. Additionally, investigation of modified laceback designs, such as the fully twisted or modified anchorage configurations described in the literature, could determine whether specific laceback types differ in their complication profiles.

The findings from this trial will be disseminated through a peer-reviewed publication in an orthodontic or dental journal irrespective of outcome, in keeping with the principles of complete and transparent clinical trial reporting. Results will also be presented at national and international orthodontic conferences. The dissemination strategy will prioritize journals offering open-access publishing options to maximize accessibility, particularly for clinicians and researchers in low-resource settings where evidence-based guidance on auxiliary use is most critically needed. A lay summary of findings will be made available to all participants upon request, consistent with the patient information and consent framework provided at enrollment.
